### Procedure

The telephone interview team will call suitable ED patients within 2 weeks of their traumatic event, and an initial telephone assessment will determine whether the individual indeed meets study criteria. After receiving verbal informed consent, subjects will be given the details of a secure Internet site, where they will be asked to fill out questionnaires. Subjects with a PCL-5 score over 33 will be telephoned for a second telephone assessment. During this assessment, the patient will be assessed with the Structured Clinical Interview for DSM-IV (SCID I) and Clinician-Administered PTSD Scale (CAPS-5). If the patient fulfills the inclusion criteria, the patient will be invited to join the RCT. Subjects who enter the trial will receive a detailed description of the study, and if interested in participating, they will sign informed consent. These clinical interviews will be carried out by the telephone interview team, who will remain blind to treatment condition.

Patients will be randomly assigned by computer to one of the two treatment arms. Assigning the participants to either treatment or control group will be done using block randomization to ensure comparable numbers of participants of same gender and same initial PTSD level in each group. Patients in the waitlist condition will fill out questionnaires via the secure Internet site once a week. These will be checked by a team member dedicated to this task, who will be able to contact these patients should a specific need arrive. Patients in the i-VR arm will receive a laptop computer, with the i-VR program loaded on. They will receive training on how to access it, and a time for the first i-VR session will be made. The five i-VR sessions will be with experienced CBT therapists; these are all clinical psychologists or clinical social workers, who have received postgraduate certification as CBT therapists. In addition, they are trained in trauma-focused CBT and have extensive experience in protocol-driven research trials. Therapists will receive weekly supervision from the PI.

Sessions will be taped with the consent of the patient, and this will be used for supervision purposes. In addition, a random 10% of sessions will be evaluated by external supervisors for fidelity to the treatment protocol.

Follow-up assessment will be conducted by the telephone interview team through clinical telephone interviews, at 2 weeks following the end of treatment, and again 6 and 12 months later (Fig. 3).

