### Sample size

Given previous research studies carried out at with this population, it is reasonable to assume that the following numbers will be applicable for this study (Shalev et al., 2011). Over 18 months, there will be 600 valid cases (that match the aforementioned inclusion and exclusion criteria). Of these, approximately 33% will have sufficient symptoms at 2 weeks posttrauma. This will give 200 valid cases, and assuming 50% attrition rate, this will leave 100 subjects, 50 in the treatment group and 50 in the waitlist control group. Assuming 30% spontaneous recovery rates in the waitlist group and 70% recovery rate in the Internet intervention, an alpha of 0.05 and power of 0.95, a total group size of 64 is needed.

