### Data analysis

Data will be stored without identifying variables. It will be analyzed using SPSS 21.0 (SPSS Inc., Chicago, IL). Descriptive statistics will be used to describe the sample in terms of demographic profiles. The main outcome variable is PTSD diagnosis according to the CAPS, at 12 months posttreatment. Secondary outcomes include the severity of PTSD symptoms and depression symptoms.

The statistical analyses will be performed on the data of those participants who had participated in the pretreatment telephonic interview and in at least one follow-up wave. The principle method of data analysis will be a conditional latent class growth modeling with covariates (Bollen & Curran, 2006) using the Mplus version 7.2 software (Muthén & Muthén, 1998–2011). This method allows for comparing the trajectories of change in each of the five outcome variables between the two experimental groups while considering for possible preexisting differences in background characteristics. If the trial results are compatible with the research hypotheses, we expect the intercepts (the initial levels) of the growth curves in both groups to be identical and the slopes in the intervention group to be steeper than in the control group, indicating larger improvement in symptoms in the former group. We will use an estimation method such as full-information maximum likelihood to take advantage of all available data in presence of missing values. In case that the data will be non-normally multivariately distributed, as tested by Mardia's statistics, we will use estimation with robust standard errors (Little & Rubin, 2002) and corrected chi-square values. In the analyses, appropriate adjustments will be made for the permuted-block design of the trial sample.

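### Equal pretreatment intercepts are listed as an expected finding although randomisation already implies them; the severity growth model should use one common pretreatment mean

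*Protocol article*

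**What the plan says.** The protocol article's Data analysis section plans a conditional latent class growth model with covariates that compares trajectories between the arms. It then describes the pattern that would agree with the hypotheses. The sentence opens "If the trial results are compatible with the research hypotheses" and continues "we expect the intercepts (the initial levels) of the growth curves in both groups to be identical"; the slopes are to be steeper under the intervention. No equality constraint on the intercepts is stated. The only covariates mentioned are background characteristics, and baseline severity is not named. An adjustment for the permuted-block design is promised without its form.

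The same section sets the role of the outcomes: "The main outcome variable is PTSD diagnosis according to the CAPS, at 12 months posttreatment", and "Secondary outcomes include the severity of PTSD symptoms and depression symptoms". The analysis set is limited to patients with the pretreatment interview and at least one follow-up wave, and missing values are to be handled by full-information maximum likelihood.

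The Procedure section puts the CAPS interview before consent and allocation, and describes "block randomization to ensure comparable numbers of participants of same gender and same initial PTSD level in each group".

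**The concern.** Two things follow if the sentence is read as written.

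- **Interpretation.** An equality built into the model is not something results may or may not show, so listing it as expected implies that each arm has its own intercept. Before allocation the two arms have the same population mean whether or not the therapy works. Observed equality therefore supports no hypothesis, and an observed gap contradicts none.
- **Estimation.** With an intercept per arm, the slope contrast behaves much like a change-score contrast. The arm that happens to start higher tends to fall more steeply with no treatment effect at all. Entering the pretreatment score as the first wave is not the same as adjusting for it.

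At stake is the precision of the estimated effects on PTSD severity and depression, and how those estimates read in a trial where a baseline gap happens to occur.

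**Working it through.** **The plan's own figure.** The Sample size section gives "Assuming 30% spontaneous recovery rates in the waitlist group and 70% recovery rate in the Internet intervention" and "an alpha of 0.05 and power of 0.95, a total group size of 64 is needed". With a pooled test of two proportions, one-sided, n per arm = [1.645·√(2·0.5·0.5) + 1.645·√(0.3·0.7 + 0.7·0.3)]² / 0.4² = (1.645 × 1.355)² / 0.16 ≈ 31.1, so 32 per arm and 64 in total. The figure reproduces one-sided; two-sided it would be 76. It concerns the binary outcome and neither supports nor refutes the present point. What carries over is the analysable number: "assuming 50% attrition rate, this will leave 100 subjects, 50 in the treatment group and 50 in the waitlist control group".

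**Inputs for the severity outcomes.** From the article: n = 50 per arm and four waves. Assumed, because the article gives no SD, correlation or curve shape:
- a single-class linear growth model, complete data and equal variances (SD = 1);
- weekly sessions, and later waves counted from the post-treatment interview, which gives t = 0, 1.6, 7.6 and 13.6 months.

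Then the mean time is 5.7, Sxx = Σ(t − 5.7)² = 115.3, Σt² = 245.3, (Σt)² = 519.8 and T = 13.6.

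**Step 1: equal correlation ρ between waves.**
- Arm-specific intercepts: Var = T² · (2/n) · (1 − ρ) / Sxx.
- Common intercept: Var = T² · (2/n) · (1 − ρ) / [Σt² − (Σt)² · ρ/(1 + 3ρ)].

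For ρ = 0.3 the second denominator is 245.3 − 519.8 × 0.3/1.9 = 163.2, so the variance ratio is 115.3/163.2 = 0.71.

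| ρ | SE, arm-specific (SD) | SE, common (SD) | Variance cut |
|---|---|---|---|
| 0.2 | 0.227 | 0.181 | 36% |
| 0.3 | 0.212 | 0.178 | 29% |
| 0.5 | 0.179 | 0.162 | 18% |
| 0.7 | 0.139 | 0.132 | 10% |

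**Step 2: random slopes.** With random-intercept variance 0.5–0.7, random-slope variance 0.2–0.5 at the last wave and no intercept–slope correlation, the cut is 5–15%. A wider grid (waves at 0, 2, 8 and 14 months, intercept share of baseline variance 0.4–0.8) depends mainly on the intercept–slope correlation: 24–38% at −0.5, 8–26% at −0.2 and about 0–13% at +0.3. So the range is about 0–35%, slightly more at the extreme corner.

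**Step 3: a simpler cross-check.** For one pre–post contrast the variances are proportional to 2(1 − ρ) with a free baseline and 1 − ρ² with a common one, a ratio of (1 + ρ)/2. At ρ = 0.5 the SE falls from 0.200 to 0.173 SD, and power for an assumed 0.5 SD effect rises from 70% to 82%.

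**Step 4: carry-over of a chance gap.** One SE of the baseline difference is √(2/50) = 0.2 SD. With no treatment effect, a gap d moves the 12-month slope effect by (5.7/115.3) · (1 − ρ) · d · 13.6. For d = 0.2 this is 0.094 SD at ρ = 0.3 and 0.067 SD at ρ = 0.5, each under half of the corresponding SE (0.212 and 0.179). With a common intercept, under the same equal-correlation assumption, the shift is zero.

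**Step 5: effect of blocking.** If initial PTSD level were blocked by a median split of normal scores (an assumption), the SE of the gap would fall from 0.20 to about 0.12 SD before attrition, and the shift to about 0.04–0.06 SD. Depression is not a blocking factor, so step 4 stands there, taking the pretreatment depression score as part of the same interview.

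**The case against.** The case against has several parts.

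- **The article never states that intercepts are free.** True in the literal sense, and a journal article may leave constraints to a fuller plan. But a plan that imposed equality would not fit the printed sentence, which treats equality as something to be seen in the results. The inference stands as an inference.
- **A reader might infer a formal success criterion.** The article does not support that. No test, threshold or decision rule is attached to the intercepts, and its interpretation of improvement rests on the slopes. A false-failure rate for an intercept test would describe a test that is not planned.
- **A reader might infer bias.** Over repeated randomisations the slope contrast is unbiased. The shift is conditional on the imbalance that occurs, and the SE already contains it, so the two should not be counted as separate harms.
- **Safeguards exist.** Blocking on initial PTSD level limits the imbalance for PTSD severity, and the promised design adjustment may bring that level into the model. Both points stand for PTSD severity; neither covers depression.
- **The numbers come from a simpler model.** Also true. The planned model has latent classes, and under random slopes with a positive intercept–slope correlation the gain can vanish. A flat claim that precision is lost would be too strong.
- **The premise weakens in the stated analysis set.** This is the most useful objection. Requiring a follow-up is a selection after randomisation, with 50% attrition assumed. Equal baseline means are guaranteed only among all randomised patients, so a common intercept should not simply be imposed on the restricted set.

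**Conclusion.** The point holds in limited form. The expectation of identical intercepts should not be offered as part of the evidence for the hypotheses, and the wording implies a model that makes poorer use of the pretreatment score than it could.

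The possible gain from a common pretreatment mean is a variance cut of about 10–36% on the 12-month slope effect under equal correlations of 0.7–0.2, and about 0–35% with random slopes. Its size rests entirely on assumed covariances, a linear slope, complete data and a single class.

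It concerns the continuous outcomes, most clearly depression. The main outcome as the Data analysis section defines it, the binary diagnosis at 12 months, is untouched, and so is the sample size. A reader should not infer that the main comparison is invalid or that the severity estimates are biased on average. The change is worth making because it is cheap.

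**What to change.** For the severity outcomes:

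1. Specify one pretreatment mean common to both arms, with arm effects entering at the follow-up waves only. Alternatively, take the pretreatment score out of the outcome series and adjust for it as a covariate.
2. Fit the model by full-information maximum likelihood, as already planned, to all randomised patients instead of only those with at least one follow-up.
3. Delete identical intercepts from the pattern expected under the hypotheses, and report pretreatment levels by arm descriptively.

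Cost: one model constraint, a change of wording and a wider analysis set. No new data and no extra patients are needed.

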**Discussion:**

The results will provide more insight into the effects of preventive interventions, in general, and Internet-based early interventions, in particular, on PTSD, in an injured population, during the acute phase after trauma. We will discuss possible strengths and limitations.

Posttraumatic stress disorder (PTSD) (American Psychiatric Association [APA], 2013) was once considered a refractory disorder but advances over the past two decades now provide patients with a variety of effective treatment options. Much research has focused on trauma-focused cognitive-behavioral therapy (CBT), which is more effective than other psychotherapies in reducing chronic PTSD, that is, PTSD that has lasted for more than 3 months (APA, 2013; Bisson et al., 2007).

Studies have shown that while most people exhibit symptoms shortly following trauma exposure, the vast majority will recover naturally (Freedman, Brandes, Peri, & Shalev, 1999). This has led to the understanding that the optimal time for intervention may be shortly after trauma exposure (Kearns, Ressler, Zatzick, & Rothbaum, 2012). A growing body of research indicates that it is possible to provide effective therapeutic interventions in this post-exposure time-period for symptomatic patients. These studies report that CBT is more effective than other treatment modalities (Bryant, Sackville, Dang, Moulds, & Guthrie, 1999), waitlist control (Sijbrandij et al., 2007), and medication (Shalev et al., 2012) in preventing PTSD. Main studies have shown that the effects found can be long lasting, with some follow-up studies showing that some patients that receive CBT remain symptom free for up to 4 years (Bryant, Moulds, & Nixon, 2003) although this is not universal.

These studies have also highlighted, however, that most people avoid treatment (Shalev, Ankri, Peleg, Israeli-Shalev, & Freedman, 2011). These individuals may not come for treatment for a variety of reasons, including stigma, concern over time lost from work, lack of locally available therapists, and lack of sufficient resources in post-disaster settings (Hoge et al., 2004).

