## Current study

The intervention used in this study—i-VR (Internet-VR)—was specifically designed as an intervention for PTSD that combines the two platforms described here, creating a VR environment that can be accessed via the Internet. Both the therapist and the patient will concurrently occupy the environment, even though they are not in the same physical place. This is illustrated in Fig. 1. The i-VR platform will be easier to access than other cyberspace environments. The intervention includes evidence-based components for PTSD, such as breathing retraining, exposure, and cognitive restructuring. It is a five session protocol, similar to those that have been used in other early intervention studies for PTSD (Bryant et al., 1999). This randomized controlled trial (RCT) will examine the following hypotheses:i-VR CBT will be more effective at reducing PTSD symptoms than the waitlist control, such that they will have lower PTSD levels at all follow-up assessments.i-VI CBT will result in less use of health services and fewer missed work days than the waitlist control.Patients who spend more time using the i-VR environment between sessions will benefit more from the treatment.

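### The expected result is worded as a steeper slope in a latent class growth model, which tests neither lower PTSD levels at every follow-up nor CAPS diagnosis at 12 months

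*Protocol article*

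**What the plan says.** The first hypothesis, under Current study, is about level: treated patients should do better such that "they will have lower PTSD levels at all follow-up assessments". The Data analysis section then makes PTSD diagnosis by CAPS at 12 months after treatment the main outcome, with symptom severity and depression secondary.

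The same section names "conditional latent class growth modeling with covariates" as the principal method. If the hypotheses are right, it expects the intercepts, defined as the initial levels, to be identical and "the slopes in the intervention group to be steeper than in the control group". It does not state the shape of growth, how time is coded, whether the intercepts are constrained to be equal, or how many classes there are. It names no arm contrast at any single follow-up and no separate test of the 12-month diagnosis.

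Under Procedure and Research tools there are four interview waves: before treatment, 2 weeks after its end, and 6 and 12 months later.

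**The concern.** Three parts of the article ask different questions. The hypothesis asks about level at each follow-up, the main outcome about diagnosis at one time point, and the described result about rate of change. A colleague holding the final data could not tell from this text which comparison decides the trial.

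The slope is a weak stand-in here because of the timing. All five sessions fall between the first and second waves, and about 12 of the roughly 13.6 modelled months lie after treatment. The introductory text says that after trauma "the vast majority will recover naturally", and the Sample size section assumes 30% spontaneous recovery on the waitlist. An early gain followed by a narrowing gap is therefore plausible, and one straight line per arm describes it poorly.

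The model is also described in two ways. A latent class model estimates data-driven subgroups, and treatment can enter through class membership or through growth within a class. One intercept and one slope per arm is a single-class growth curve. These are different analyses, and with about 100 patients expected the first may depend on the number of classes chosen.

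**Working it through.** **The plan's own figure.** The Sample size section says: "Assuming 30% spontaneous recovery rates in the waitlist group and 70% recovery rate in the Internet intervention", with "an alpha of 0.05 and power of 0.95, a total group size of 64 is needed". For two proportions with pooled variance under the null, n per arm = [z_α·√(2·0.5·0.5) + 1.645·√(0.3·0.7 + 0.7·0.3)]² / 0.4². One-sided (z_α = 1.645) this is 31.05, so 32 per arm and 64 in total, which reproduces the figure. Two-sided (1.96) it is 37.6, so 38 per arm and 76 in total. Either way it sizes a comparison of recovery proportions, not a slope.

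**Assumptions not in the article.** Straight-line time in months; free intercepts; complete data; weekly sessions, so the first follow-up is 7 weeks (1.61 months) after baseline and the waves are at t = 0, 1.61, 7.61 and 13.61; unit SD; equal correlation ρ between waves. The 50 per arm is from the Sample size section ("50 in the treatment group and 50 in the waitlist control group").

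Mean t = 22.83/4 = 5.7075. Sxx = Σ(t − mean)² = 115.43. Slope = Sxy/Sxx.

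**Fading effect.** Illustrative mean CAPS scores:

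| Arm | Scores at the four waves | Sxy | Slope per month | Intercept |
|---|---|---|---|---|
| i-VR | 35, 20, 19, 18 | −103.32 | −0.895 | 28.1 |
| Waitlist | 35, 31, 26, 22 | −103.465 | −0.896 | 33.6 |

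i-VR is better by 11, 7 and 4 points, yet the slopes agree and a gap of 5.5 appears in the fitted intercepts. With the first follow-up at 2.5 months the slopes are −0.903 and −0.866, still close.

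**Sustained effect.** For a true difference of (0, d, d, d):
- slope difference = 5.7075d/115.43 = 0.0494d per month
- intercept difference = 0.75d − 0.0494d × 5.7075 = 0.47d
- slope-driven difference at the last wave = 0.0494d × 13.61 = 0.67d

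With the first follow-up at 2.5 months the last two are 0.43d and 0.73d; with equally spaced waves, 0.30d and 0.90d.

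**Power at d = 0.5, 50 per arm, ρ = 0.5, two-sided 0.05.**
- Slope: SE = √[2(1 − ρ)/(n·Sxx)] = √[1/(50 × 115.43)] = 0.01316; z = 0.0247/0.01316 = 1.88; power = Φ(1.88 − 1.96) = 0.47.
- Baseline-adjusted 12-month contrast: SE = √[2(1 − ρ²)/n] = √(1.5/50) = 0.173; z = 2.89; power = Φ(0.93) = 0.82.
- For ρ = 0.3 / 0.5 / 0.7: slope 0.35 / 0.47 / 0.68; contrast 0.75 / 0.82 / 0.94.

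**Power at the planned effect.** 30% against 70% corresponds to 0.524 + 0.524 = 1.05 SD on the probit scale. Slope power with 50 per arm is 0.91 / 0.98 / over 0.99 for the three correlations; with 32 per arm it is 0.76 / 0.88 / 0.98.

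**Intercepts held equal.** For the sustained effect (d = 0.5, ρ = 0.5, 50 per arm) slope power recovers to 0.77, or 0.82 with the first follow-up at 2.5 months. For the fading example, whose true 12-month gap is 4 points, the model-implied gap is 6.9, 3.8, 2.4 and 1.3 at ρ = 0, 0.3, 0.5 and 0.7. The constraint restores power but does not reliably recover the 12-month difference.

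**The case against.** The strongest reply is that linear time in months is not in the article, which condenses a fuller plan that may fix the time shape. This stands and limits the numerical part. With waves coded 0 to 3, the fading example gives −5.2 for i-VR against −4.4 per wave, so i-VR is steeper. A piecewise model would also see the early gain: (20 − 35)/1.61 = −9.3 against (31 − 35)/1.61 = −2.5 per month. The mismatch between hypothesis, main outcome and described result does not depend on time shape.

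A reader might go further and infer any of the following. The documents do not support them.

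- *The steeper slope is the formal criterion for success.* The text words it as an expected pattern, not a decision rule. It is, however, the only pattern that the section ties to the hypotheses.
- *An early gain that plateaus vanishes into the intercept.* With the pretreatment wave in the model the absorption is partial, 30% to 47%. A slope difference near zero needs an effect that fades. A fitted intercept gap between randomised arms would also contradict the expectation of equal initial levels and so warn of misfit.
- *The waitlist could win on slope.* Means of 35, 31, 24, 18 against 35, 20, 18, 18 for i-VR do give −1.203 against −0.912. But both arms end at 18, so this is not a missed 12-month effect.
- *The normality check is a serious flaw.* The robust option applies "In case that the data will be non-normally multivariately distributed". A test of multivariate normality suits a binary outcome badly, but a rejecting test already leads to robust errors, so this is minor.

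**Conclusion.** The point holds as a mismatch that should be fixed, with medium confidence. The slope comparison described does not test the level claim in hypothesis 1 or the 12-month diagnosis, and the model named is not the model described. That much rests on the text alone.

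The size is conditional on linear calendar time, free intercepts and the assumed correlations. Under these, the cost is large for a moderate sustained effect, and a fading effect can leave almost no slope difference. At the planned 30% against 70% with 50 per arm, slope power stays at 0.91 or more, so the documents do not support saying that the trial would probably miss the effect it was sized for. How far the number of classes would change the answer was not quantified.

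**What to change.** - **Primary contrast:** the arm difference in CAPS diagnosis at 12 months, from a binary model such as logistic regression adjusted for gender and initial PTSD level, the two factors that the randomisation balances.
- **Scores:** analyse CAPS-5, PCL-5 and BDI with a single-class repeated-measures model that has visit as a categorical factor, arm-by-visit terms and a common baseline mean. Report the arm difference at each follow-up, which answers hypothesis 1 directly.
- **Exploratory only:** latent classes and slope comparisons. If they are kept, state the time coding, the growth shape and the rule for choosing the number of classes.

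This changes wording only and runs in standard software. The price is a few more mean parameters than a straight line, and some power if the true arm difference really grows linearly. The change should be made before unblinded data are seen, so that neither time shape nor class number is chosen afterwards.
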